### Outcome measures

**Primary outcome measures**: The outcome measures for our primary objective will include HF HRV, LF SBPV, BRS, HR, and BP during supine assessments, FCT, and SUT, both pre- and post-a single bout of HIIE.

**Secondary outcome measures**: The outcome measures for our secondary objective will include CBFV during cognitive testing and cognitive performance assessed pre- and post-a single bout of HIIE.

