### Sample size calculation

A pilot study was conducted to guide the design of this research. Based on the pilot data, we plan to recruit up to 20 participants per group, accounting for an estimated 20% attrition rate [40], to ensure at least 15 participants with complete data to be included in the analyses for sufficient statistical power (β ≥ 80%, α = 0.05). This sample size is calculated based on using a two-sample two-sided t-test to detect significant differences between the SCI and control groups for the change from baseline in ANS-CV function. High-frequency heart rate variability (HF HRV) reflects parasympathetic activity, with normalized units accounting for changes in total power during autonomic activation [41–43]. Similarly, low-frequency systolic blood pressure variability (LF SBPV; Mayer waves) serves as a biomarker of sympathetic vasomotor control [44]. Based on the pilot study, the estimated minimum detectable effect sizes are 24.97 for the difference in normalized HF HRV and 3.52 mmHg² for the difference in LF SBPV between groups, which are the two primary ANS-CV variables.

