### Data analysis

To analyze the impact of HIIE on cardiovascular, cerebrovascular, and cognitive functions in individuals with SCI compared to controls, linear mixed-effects models (LMMs) will be utilized. These models will assess the main effects and interactions of group (SCI vs. controls) and time (pre-HIIE vs. post-HIIE) across different outcomes, with specific adjustments tailored to the type of function being analyzed. The general model can be structured as follows:

Y_ij_ = β_0 _+ b_i_ + β_1_Group_i_ + β_2_Time_j _+ β_3_Group_i _× Time_j _+ β4 × Covariates_i _+ ∊_ij_

Where:

Y_ij_ represents the dependent variable (e.g., HR, BP, HF HRV, LF SBPV, BRS) for subject *i* at time j (j = 0,1).Group_i_ is the SCI/control status for subject *i* (SCI: Group_i _= 1, Control: Group_i_ = 0).Time_j_ is the *jth* time point (pre-HIIE: Time_j_ = 0, post-HIIE: Time_j_ = 1).Covariates_i_ are additional covariate(s) for subject *i*. For dependent variables within cardiovascular and cerebrovascular functions: baseline physical activity levels. For cognitive function: pre-morbid intelligence and psychological distress.b_i_ is the random effect for subject *i* to account for within-subject correlation over time and is assumed independent N(0, σ_b_^2^).∊_ij_ is the residual error term assumed independent N(0, σ_∊_^2^).

Estimation of parameters will be analyzed by restricted maximum likelihood estimation (REML). Wald tests will be used to assess the significance of the predictors, with the significance level set at p < 0.05. All analyses will be conducted using RStudio (© 2009–2024 Posit Software, PBC).

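### The sample size rests on two primary variables in an unnamed test condition, but the outcome section makes five measures primary in three conditions, each tested at p < 0.05 with no family-wise control stated

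*Protocol article*

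**What the plan says.** Three sections of the protocol article bear on this.

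- **Sample size calculation.** The study is sized by "using a two-sample two-sided t-test to detect significant differences between the SCI and control groups for the change from baseline in ANS-CV function", at α = 0.05 and 80% power with 15 completers per group. The detectable differences are "24.97 for the difference in normalized HF HRV and 3.52 mmHg² for the difference in LF SBPV between groups", and the section adds of these variables: "which are the two primary ANS-CV variables". It does not say whether they refer to supine rest, the face-cooling test (FCT) or the sit-up test (SUT), and it gives no standard deviation.
- **Outcome measures.** The primary list is longer: "The outcome measures for our primary objective will include HF HRV, LF SBPV, BRS, HR, and BP during supine assessments, FCT, and SUT", before and after exercise. No order or priority is given. The list says HF HRV without stating whether the raw or the normalized form is meant; the Equipment section defines both.
- **Data analysis.** One general mixed model with Group, Time and Group × Time is given for each dependent variable, with no term for test condition. The decision rule is: "Wald tests will be used to assess the significance of the predictors, with the significance level set at p < 0.05".

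**The concern.** The two definitions of the primary family cannot both hold. Two variables were sized; five measures in three conditions are called primary. Because the model has no condition term, the natural reading is a separate fit for each measure in each condition.

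Two things are at stake. First, a reader of the eventual report cannot tell which result decides the primary objective, so any one of a long list could be presented as the primary success. Second, the power statement supports only part of the list.

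The unnamed condition matters in its own right. The Experimental procedure section uses FCT to activate the parasympathetic system and SUT to activate the sympathetic system, so what a given difference in HF HRV or LF SBPV means depends on the condition in which it is measured.

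**Working it through.** **Inputs.** From Sample size calculation: two-sided two-sample t-test on change, α = 0.05, power 80%, n = 15 completers per group, detectable differences 24.97 (HF HRV, n.u.) and 3.52 mmHg² (LF SBPV), 20% attrition, up to 20 recruited per group. From Outcome measures: 5 measures, 3 conditions. From Data analysis: 0.05 per test. The SD of change is not given and is back-solved below; that is an assumption.

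**1. The plan's own figure.** With df = 28 the critical value is 2.048. Power is P(|T| > 2.048), where T is noncentral t with noncentrality d·√(15/2). Setting power to 0.80 gives d = 1.060. The implied SDs of change are
- HF HRV: 24.97 / 1.060 = 23.6 n.u.
- LF SBPV: 3.52 / 1.060 = 3.32 mmHg²

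Without a stated SD, the 15 per group cannot be reproduced independently; it is consistent with these values. The recruitment step does reproduce: 15 / 0.80 = 18.75, so 19, within the planned maximum of 20.

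**2. Size of the primary family.** Sample size calculation: 2 variables. Outcome measures, read literally: 5 × 3 = 15 combinations, counting BP as one measure and one Group × Time test each.

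**3. Chance of at least one false positive, each test at 0.05.** If independent, this is 1 − 0.95^k:
- k = 2: 1 − 0.95² = 9.75%
- k = 15: 1 − 0.95¹⁵ = 53.7%

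For 15 two-sided z-tests with a common correlation:

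| Correlation | At least one false positive |
|---|---|
| 0 | 54% |
| 0.3 | 46% |
| 0.5 | 36% |
| 0.7 | 26% |
| 0.9 | 14% |

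**4. Two primaries at 0.025 each** (Bonferroni, which is also the first Holm step). The critical value is 2.368.
- Power at d = 1.060: 70.2%
- d needed for 80% power: 1.179
- HF HRV: 24.97 × 1.179 / 1.060 = 27.8 n.u.
- LF SBPV: 3.52 × 1.179 / 1.060 = 3.92 mmHg²

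**5. Power per variable under Holm**, if both effects are real at d = 1.060 and the tests are independent. A variable is rejected if its p-value is below 0.025, or if it lies between 0.025 and 0.05 and the other variable's is below 0.025:

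0.702 + (0.800 − 0.702) × 0.702 = 0.771, about 77%.

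**The case against.** **The analysis plan is not shown.** Multiplicity procedures are often left to a statistical analysis plan, and a journal article is condensed. That stands as far as the procedure goes: a missing adjustment alone would not be a finding. It does not cover the conflict between two sections of the same article over what is primary. An analysis plan would have to choose between them before it could adjust anything.

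**The study is exploratory.** The Discussion says that it cannot settle definitive efficacy endpoints and that the direction and pattern of responses will be considered. No section says that a single significant result makes the primary objective positive. This is fair, so the false-positive figures are conditional on that rule. But the article also labels outcomes primary, states directional hypotheses, claims 80% power and sets a significance threshold, and those need one consistent primary definition.

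**The count is not firm.** The Cardiovascular function section lists BP, HR, HRV and SBPV for FCT and SUT but not BRS, which would give 13 combinations (1 − 0.95¹³ = 49% if independent). The count would rise if BP means several pressures. Fifteen is the literal reading of the outcome section, not a guaranteed minimum.

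**Stronger readings that a reader might infer.** One is that the plan has no error control at all. It does not say that: each test is held at 5%, and what is not stated is family-wise control. Another is that the 80% power is void for the primary objective. Both sized variables are on the primary list, so the power statement still applies to each singly. A third is that the study's false-positive rate is 54%. That needs independence, which is implausible for measures drawn from the same signals and participants.

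**Conclusion.** The point holds. The article defines its primary family in two incompatible ways, leaves the condition behind its detectable differences unnamed, and fixes a 0.05 threshold per test with no family-wise control stated. The 80% power is limited to normalized HF HRV and LF SBPV, taken one at a time, unadjusted, in one unnamed condition. It is not demonstrated for BRS, HR, BP or the whole set.

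Under an any-one-significant reading of 15 Group × Time tests, the family-wise rate runs from about 14% (correlation 0.9) to 54% (independence), above 5% throughout that range. These figures assume equal correlations and the literal count of 15. The power figures assume the back-solved SDs and 15 completers per group.

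**What to change.** By a dated amendment, made before outcome data are analysed, bring the outcome section into line with the sample size section.

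- **Primary:** normalized HF HRV and LF SBPV, each in one named condition (the one behind its stated detectable difference). Use the Group × Time contrast, with Holm adjustment to 0.05 overall.
- **Secondary:** BRS, HR, BP and the remaining conditions, reported with confidence intervals.
- **Sizing:** restate at the first Holm step (0.025) and label it conservative. Give either about 70% power at 24.97 n.u. and 3.52 mmHg², or detectable differences of about 27.8 n.u. and 3.92 mmHg² at 80% power. Add that power per variable under Holm is about 77% if both effects are real and independent. State the pilot SDs and condition so that the figures can be checked.

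Another explicit rule, such as a fixed testing order, would also remove the conflict, provided power is restated to match.

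The cost is a less favourable stated power or detectable difference, an IRB-approved amendment and a registry update. Because recruitment has begun and data collection is described as ongoing, the amendment should state that outcome data did not guide the choice. No added participants or measurements are needed.

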### Data analysis

To analyze the impact of HIIE on cardiovascular, cerebrovascular, and cognitive functions in individuals with SCI compared to controls, linear mixed-effects models (LMMs) will be utilized. These models will assess the main effects and interactions of group (SCI vs. controls) and time (pre-HIIE vs. post-HIIE) across different outcomes, with specific adjustments tailored to the type of function being analyzed. The general model can be structured as follows:

Y_ij_ = β_0 _+ b_i_ + β_1_Group_i_ + β_2_Time_j _+ β_3_Group_i _× Time_j _+ β4 × Covariates_i _+ ∊_ij_

Where:

Y_ij_ represents the dependent variable (e.g., HR, BP, HF HRV, LF SBPV, BRS) for subject *i* at time j (j = 0,1).Group_i_ is the SCI/control status for subject *i* (SCI: Group_i _= 1, Control: Group_i_ = 0).Time_j_ is the *jth* time point (pre-HIIE: Time_j_ = 0, post-HIIE: Time_j_ = 1).Covariates_i_ are additional covariate(s) for subject *i*. For dependent variables within cardiovascular and cerebrovascular functions: baseline physical activity levels. For cognitive function: pre-morbid intelligence and psychological distress.b_i_ is the random effect for subject *i* to account for within-subject correlation over time and is assumed independent N(0, σ_b_^2^).∊_ij_ is the residual error term assumed independent N(0, σ_∊_^2^).

Estimation of parameters will be analyzed by restricted maximum likelihood estimation (REML). Wald tests will be used to assess the significance of the predictors, with the significance level set at p < 0.05. All analyses will be conducted using RStudio (© 2009–2024 Posit Software, PBC).

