**Results:**

We hypothesize that HIIE will improve cardiovascular and cerebrovascular functions and enhance cognitive performance in the SCI group. Data will be analyzed using linear mixed-effects models to evaluate the interaction effects of group and exercise.

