### Measurements and tests

#### Physical activity and psychological distress questionnaire.

Physical activity will be assessed using the International Physical Activity Questionnaire-Short Form (IPAQ-SF) developed for the non-injured control group and the Leisure Time Physical Activity Questionnaire, which was developed specifically for People with SCI (LTPAQ-SCI) for the SCI group. The IPAQ-SF evaluates physical activity over the past 7 days, capturing vigorous, moderate, and walking intensities, as well as sedentary behavior, providing a comprehensive activity profile [67]. The LTPAQ-SCI is an SCI-specific tool measuring mild, moderate, and heavy intensity leisure-time physical activity over the same period, with a structure similar to the IPAQ-SF [68,69]. Both self-administered questionnaires are validated, widely used, and take less than 5 minutes to complete [67–69]. Psychological distress will be evaluated using Hospital Anxiety and Depression Scale (HADS) designed to identify symptoms of anxiety and depression in both the general population and individuals with SCI [70–72]. The HADS consists of 14 items, evenly divided into two subscales: anxiety (HADS-A) and depression (HADS-D). Each subscale contains 7 items, with participants rating their experiences over the past week on a 4-point Likert scale. This tool provides a reliable and efficient evaluation of psychological distress, making it suitable for use in clinical and research settings [70–72].

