This study protocol addresses these gaps by focusing on the acute effects of HIIE, a short-duration yet high-impact exercise modality, on ANS-CV, cerebrovascular, and cognitive outcomes in individuals with SCI at or above T6. Unlike previous exercise studies in SCI [12,21,22], this protocol incorporates sensitive ANS-CV tests, such as the SUT and FCT, rather than relying solely on resting conditions. This approach provides a more dynamic and comprehensive understanding of how HIIE influences physiological and cognitive functions in this population. Furthermore, this study incorporates critical covariates (i.e., physical activity levels, pre-morbid intelligence, and psychological distress) to ensure robust and nuanced analyses. By addressing these variables, the study aims to generate findings that are both clinically relevant and generalizable. This approach is particularly innovative, as previous studies have largely overlooked the interplay between these covariates and exercise-induced physiological changes in the SCI population.

The implications of this research extend beyond the immediate outcomes. By demonstrating the feasibility and potential benefits of HIIE, this protocol sets the stage for larger, long-term studies that aim to refine exercise prescriptions for individuals with SCI. Additionally, the use of advanced physiological monitoring techniques could pave the way for more personalized exercise interventions tailored to the unique needs of each individual, based on their ANS-CV, cerebrovascular, and cognitive profiles.

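### Covariates entered only as subject-level main effects leave the Group × Time effect unadjusted, and scoring activity on a different questionnaire in each group distorts the adjusted group main effect

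*Protocol article*

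**What the plan says.** The Data analysis section gives a linear mixed model with Group, Time (pre, post), Group × Time, a random intercept per participant, and a single covariate term, β4 × Covariates_i, indexed by participant only. No product of a covariate with Time or with Group appears. On content it says: "For dependent variables within cardiovascular and cerebrovascular functions: baseline physical activity levels". For cognition the covariates are pre-morbid intelligence (NAART) and psychological distress (HADS). The section says that main effects as well as interactions will be assessed.

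The section on the physical activity questionnaire names the instruments: "International Physical Activity Questionnaire-Short Form (IPAQ-SF) developed for the non-injured control group and the Leisure Time Physical Activity Questionnaire", the second being for the SCI group. The IPAQ-SF takes in walking and sedentary behaviour; the LTPAQ-SCI covers leisure-time activity only. The section calls their structure similar but gives no common score.

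The target is the difference in response. The Abstract says: "Data will be analyzed using linear mixed-effects models to evaluate the interaction effects of group and exercise". The sample size rests on "using a two-sample two-sided t-test to detect significant differences between the SCI and control groups for the change from baseline in ANS-CV function", with "at least 15 participants with complete data to be included in the analyses".

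The Discussion says: "this study incorporates critical covariates (i.e., physical activity levels, pre-morbid intelligence, and psychological distress) to ensure robust and nuanced analyses". It then presents as innovative that the study looks at how these covariates and the physiological changes after exercise act together.

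**The concern.** Two features of the printed model do not do what the text around it says.

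- **Exercise response.** A covariate that is constant within a participant can explain why one person's level is higher than another's. It cannot explain why one person changes more than another. A paper following this plan could report covariate-adjusted exercise effects that are numerically the unadjusted ones.
- **Group main effect.** Activity is the only covariate for the primary cardiovascular outcomes and for the cerebrovascular outcomes. Its scores come from a different instrument in each group and share one coefficient. The model reads any difference between instruments as a difference in activity and corrects the group effect for it.

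**Working it through.** **The plan's own figure.** With 15 per group, two-sided α 0.05 and 80% power, the detectable standardised difference is 1.060 (noncentral t), or (1.960 + 0.842) × √(2/15) = 1.023 (normal approximation). The stated 24.97 n.u. then implies a change-score SD of 24.97/1.060 = 23.6 to 24.97/1.023 = 24.4. The stated 3.52 mmHg² implies 3.32 to 3.44. These SDs are not printed, so the figures cannot be reproduced, but they fit a single t-test on change. That test corresponds to β3, and nothing below alters the sample size.

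**Step 1: the covariate cancels.** Subtract pre from post in the printed model:

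Y_i1 − Y_i0 = β2 + β3 × Group_i + (ε_i1 − ε_i0)

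Both b_i and β4 × Covariates_i drop out. With complete pairs, β3 is the difference in mean change.

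REML fits to simulated data (15 + 15 participants, two time points, assumed parameters) agree:

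- In one data set β3 = −1.2833 (SE 0.4819) with no covariate, a common-scale covariate, a two-instrument covariate, or group-specific slopes. The t-test on change gives the same estimate and SE.
- Over 300 data sets a main-effect covariate moved β3 by at most 4 × 10⁻¹⁵ and its SE by at most 1.5 × 10⁻⁵, which is numerical noise.
- In one data set with about 20% of post values missing, the cancellation was only approximate: β3 was −0.884 without a covariate, and −0.883 (common scale) or −0.932 (two instruments) with one.

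**Step 2: one slope over two instruments.** Assume equal true activity in both groups (mean μ, SD s), the same slope γ on the outcome, no true group difference, and a control score k times the SCI score.

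- Pooled within-group slope: γ(1 + k)/(1 + k²), in SCI score units.
- Difference in mean score, SCI minus control: μ(1 − k).
- Adjusted β1 = 0 − γ(1 + k)/(1 + k²) × μ(1 − k) = γμ(k² − 1)/(k² + 1).
- In outcome SDs, with γ = r × SD_Y/s: r × (μ/s) × (k² − 1)/(k² + 1).

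The last factor is 3/5 = 0.600 for k = 2, 24/26 = 0.923 for k = 5, and 143/145 = 0.986 for k = 12. The documents give none of r, μ/s or k, so all are assumptions:

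| r | μ/s | k = 2 | k = 5 | k = 12 |
|---|---|---|---|---|
| 0.20 | 1.00 | 0.12 | 0.18 | 0.20 |
| 0.58 | 1.00 | 0.35 | 0.54 | 0.57 |
| 0.58 | 1.43 | 0.50 | 0.77 | 0.82 |

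Entries are spurious β1 in outcome SDs. Simulation gave 0.11, 0.18 and 0.18 for the first row and 0.48, 0.77 and 0.82 for the last.

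**Step 3: what a Covariate × Time term would do.**

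- *Raw two-instrument score.* The algebra of step 2 then applies to the change, so the distortion enters β3. In one simulated data set β3 went from 0.385 without the term to 0.932 with it, against 0.445 when the true activity score was used.
- *Activity standardised within group.* The score has mean zero in each group, so the β3 estimate cannot move; only its SE can. In two fits the SE fell from 0.363 to 0.351 (3.3%) and from 2.559 to 2.419 (5.5%).

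**The case against.** The strongest reply is that the contrast the trial is built on is sound. β3 equals the difference in mean change, which is what the sample size section powers, and the hypotheses in the Introduction concern response to exercise rather than baseline group differences. This stands. A reader might infer that the primary contrast is biased by the two questionnaires; the printed model has no Covariate × Time term, so it is not.

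A reader might also infer that the covariate adjustment fails altogether. It does not. NAART and HADS are the same instruments in both groups and validly adjust the group main effect for cognition. The Introduction says only that covariates account for individual variability, which a main effect does for outcome level. The conflict is with the Discussion's claim about exercise-induced changes.

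It can further be said that the model is introduced as a general form, that neither questionnaire's scoring unit is given, and that harmonisation may be left to an analysis plan. This stands in part: the difference in content is documented, while the difference in numerical scale is assumed. Still, the article prints one coefficient for one activity covariate, and similar structure does not make the scores comparable. It also says that main effects will be assessed, so β1 is a reported result even without a hypothesis attached.

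**Conclusion.** The point holds in two limited parts.

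1. As printed, the covariates do not adjust the Time or Group × Time effects. This is exact for complete pairs (for the SE, given a positive random-intercept variance) and approximate when post values are missing. β3 is unbiased but is an unadjusted estimate and should be described as such.
2. For cardiovascular and cerebrovascular outcomes, the activity-adjusted β1 cannot be interpreted, because instrument and group coincide. If raw scores are entered, the distortion is about 0.1 to 0.2 outcome SDs with r = 0.2 and μ/s = 1, and about 0.5 to 0.8 with r = 0.58 and μ/s near 1.4, for k from 2 to 12. These figures also assume equal true activity and a purely multiplicative scale difference. They show a possible range, not an estimate for this trial.

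This should be corrected before analysis; it does not threaten the powered comparison.

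**What to change.** - Do not enter the raw scores of the two questionnaires under one slope. Standardise activity within each group, with a group-specific slope if wanted. State that between-group differences in activity cannot be adjusted for with two instruments.
- If the covariates are meant to bear on the exercise response, add Covariate × Time: the within-group score for activity, and NAART and HADS for cognition. For activity, say in advance that the β3 estimate will not change and that any gain is a modest one in precision.
- Do not add Covariate × Time with the raw two-instrument score, which would bias β3.
- If no such term is added, state that the covariates adjust outcome level only, and bring the Discussion's claim into line.

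The cost is a change of wording and one or two residual degrees of freedom, out of 30 − 2 = 28 for the change comparison with 15 completers per group. No new data are needed.

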**Methods:**

In this prospective case-control study, 15 individuals with SCI at T6 or above and 15 age- and sex-matched uninjured controls will be assessed. Measures include heart rate, heart rate variability, blood pressure, systolic blood pressure variability, cerebral blood flow velocities, and cognitive performance, analyzed pre- and post-HIIE. The sit-up test and face-cooling test will be used to activate the ANS-CV system. Post-exercise assessments will begin 5 minutes after completing the HIIE session. Cardiovascular testing will be conducted first and is expected to last 36 minutes. Cerebrovascular and cognitive testing will follow, starting approximately 41 minutes after the HIIE session. Covariates such as physical activity levels, pre-morbid intelligence, and psychological distress will be considered. This study has been approved by the University at Buffalo Institutional Review Board (IRB) (Approval Number: MOD00013354) and registered on ClinicalTrials.gov (Registration Number: NCT06274658).

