## Methodology

### Study design

This is a case-control study that includes a group of individuals with SCI and a sex- and age-matched uninjured control group to examine the effects of injury on exercise responses. The study protocol includes one initial visit for consent and maximal exercise testing (Visit 1) and one experimental visit (Visit 2) during which participants are exposed to a single session of HIIE. Fig 1 illustrates the schedule of enrollment, assessment, and intervention for the study (Fig 1).

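### Age and sex are used to match the controls but are absent from the model; adding them is a cheap gain for group level contrasts, and for Group×Time only through their interactions with time

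*Protocol article*

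**What the plan says.** The abstract's Methods paragraph states that "15 individuals with SCI at T6 or above and 15 age- and sex-matched uninjured controls will be assessed". Study design repeats the matching: "a sex- and age-matched uninjured control group to examine the effects of injury on exercise responses". Neither place says whether matching is one-to-one or by group. Participants admits ages 18 to 75 in both groups.

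Sample size calculation takes the groups as independent samples: "This sample size is calculated based on using a two-sample two-sided t-test to detect significant differences between the SCI and control groups" on change from baseline, with 15 analysed per group.

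Data analysis gives a mixed model with group, time, their interaction, a subject random intercept and covariates. It plans to assess main effects as well as interactions. The covariates are listed by type of outcome: "For dependent variables within cardiovascular and cerebrovascular functions: baseline physical activity levels", and pre-morbid intelligence with psychological distress for cognitive outcomes. Age, sex and a matched-pair term do not appear.

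Under Cognitive function, the Stroop and CVLT-III scores are normed for age and education. SDMT and COWAT are scored as raw counts.

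**The concern.** Balancing two groups on a prognostic variable reduces the true variance of the difference between their means. A model that leaves the variable in the error term still estimates the larger variance of unmatched groups. The reported standard error is then too large, and the test rejects less often than its nominal 5% when there is no difference. The study does the work of matching at recruitment but does not collect the precision at analysis. With 15 per group and ages from 18 to 75, that could matter. How much depends on which contrast is meant.

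**Working it through.** **1. The plan's own figure.** Inputs from Sample size calculation: n = 15 per group, two-sided α = 0.05, 80% power, detectable differences 24.97 (normalized HF HRV) and 3.52 mmHg² (LF SBPV). No SD is printed, so the power cannot be reproduced independently; it can only be worked back. With noncentrality d·√(n/2) and 28 df, 80% power needs d = 1.060. The implied SDs of change are 24.97/1.060 = 23.56 and 3.52/1.060 = 3.32 mmHg².

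**2. What age and sex main effects do to Group×Time.** In the plan's model each person's change is

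Y_i1 − Y_i0 = β2 + β3·Group_i + (ε_i1 − ε_i0).

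The random intercept and every time-constant covariate cancel. With complete pre/post data, age and sex main effects therefore cannot alter the estimate of β3 or, in substance, its standard error. A simulation of 150 matched datasets fitted by REML, with strong age and sex effects on level assumed, shows this:

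| Mean SE | Plan's model | Plus age and sex | Plus pair intercept |
|---|---|---|---|
| Group (level) | 0.521 | 0.453 | 0.451 |
| Group×Time | 0.3544 | 0.3544 | 0.3543 |

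The Group×Time estimates agree to about 10⁻¹⁵. The level contrast gains 1 − 0.453/0.521 = 13%, but only under the assumed strong effects.

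**3. What time interactions can do.** Adding Age×Time and Sex×Time makes the Group×Time test equivalent to regressing change on group, age and sex, with 30 − 4 = 26 df instead of 30 − 2 = 28. If age and sex explain a share R² of the variance of change, the noncentrality is d·√(n/(2(1 − R²))). For R² = 0/0.05/0.10/0.20/0.30 this gives power 79.8/81.8/83.8/87.8/91.6%.

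This formula does not show how the unadjusted test behaves in matched groups, so that was simulated. Assumptions: 15 per group, age uniform over 18 to 75, match error SD 3 years, d = 1.06, least squares with a t reference.

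| Variance of change explained (assumed) | Power unadjusted | Power adjusted | Size unadjusted | Size adjusted |
|---|---|---|---|---|
| 0% | 79% | 79% | – | – |
| 5% | 80% | 82% | – | – |
| 10% | 81% | 83% | 3.7% | 4.8% |
| 20% | 82% | 87% | 3.1% | 5.2% |
| 30% | 84% | 91% | 2.1% | 5.0% |

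Figures are good to about a point; with 8,000 datasets the Monte Carlo standard error at 80% is √(0.8 × 0.2/8000) = 0.4 points. Unadjusted power rises slightly because matching lowers the true variance. Adjustment recovers the rest.

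**4. Cost if the covariates explain nothing.** The detectable effect at 80% power goes from 1.060 SD (28 df) to 1.063 (26 df), or 1.066 if 4 df are counted. In the plan's units, 1.063 SD is 24.97 × 1.063/1.060 = 25.04 for HF HRV and 3.52 × 1.063/1.060 = 3.53 mmHg² for LF SBPV.

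**The case against.** The strongest reply is that the study is sized on the difference in change, for which the omitted main effects are irrelevant. A reader might infer from the matching that the primary contrast's error bars are too wide as planned. The documents do not support that: step 2 shows that effects on level cancel. A gain needs age or sex to predict the response to one 10-minute session, and nothing in the article shows that they do. At 5 to 10% explained the gain is only about two points of power. This part of the reply stands.

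A reader might also infer that ignoring the matching biases the results, especially as the design is called case-control. Participants are selected on injury status, not on an outcome, and the contrasts are differences in means. While the groups stay balanced on age and sex, leaving them out costs precision and does not shift the estimate.

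A third tempting reading is that the analysis and the sizing should be paired. One-to-one matching is not stated, and dropout would break pairs. With 15 pairs the df fall from 28 to 14, and power is 77.0% if the within-pair correlation of change is zero. Pairing breaks even at a correlation of about 0.07, which the documents do not give.

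Two further limits stand. The simulated sizes use a t reference, whereas the plan specifies Wald tests. Under a normal reference, at 20% explained, unadjusted size is 4.1% and adjusted size 6.1%, so the conservatism shrinks and the adjusted test is slightly liberal. Also, Stroop and CVLT-III are already age-normed, so there is little to gain from age there.

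Finally, the article presents a general model, and a fuller analysis plan may add to it. That supports treating the point as an improvement. It does not remove it, because the article names its covariates explicitly and leaves out the matching variables.

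**Conclusion.** The point holds as a cheap improvement, not an error. For the planned group main effect and other level contrasts, leaving out age and sex makes standard errors too large and tests conservative, to the extent that either is prognostic; 13% is an illustration under strong assumed effects. For Group×Time the main effects change nothing. Interactions with time give a gain that runs from none (0% of the variance of change explained) to about 5 points of power at 20% and 7 at 30%. The explained share, the age distribution and the match error are assumptions. The precision is nearly free rather than free. The unpaired sizing can stand: it claims no gain from the matching, and is conservative if age or sex predicts the change.

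**What to change.** In Data analysis, add age and sex to Covariates_i, with pre-specified Age×Time and Sex×Time terms, for the cardiovascular and cerebrovascular outcomes and for SDMT and COWAT. For the age-normed Stroop and CVLT-III scores, add sex only or leave the model as it is. State whether matching is one-to-one or by group. Leave the sample size as it is.

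No new data are needed beyond the variables used for matching. The cost is a change of wording and about 2 df per contrast. Study status describes data collection as ongoing, so the terms should be fixed before the outcome data are analysed.
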